# Efficacy of electrical stimulation combined with ultrasound acupuncture therapy on treatment in patients with intrauterine adhesions: Study protocol for a placebo-controlled, single-blind, single-center, randomized trial

**DOI:** 10.1097/MD.0000000000031469

**Published:** 2022-12-16

**Keywords:** electrical stimulation, intrauterine adhesions, study protocol, ultrasound acupuncture

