## Abstract

**Methods::**

This study is a single-center, randomized controlled trial. A total of 210 patients with IUAs will be randomly assigned into 2 groups according to the ratio of 1:1, as the treatment group and the control group. Participants will receive the electrical muscle stimulation combined with ultrasound acupuncture therapy and oral hormone supplementation or receive oral hormone supplementation only. The primary outcome was the clinical response rate. There were 3 menstrual cycles of treatment and 3 menstrual cycles of follow-up in this study.

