### 2.2. Study design

This is a randomized, single-center clinical trial which aimed to evaluate the effectiveness of electrical stimulation combined with ultrasound acupuncture to treat IUAs. This randomized trial was conducted in one single center: Guangxi reproductive hospital. A total of 210 patients diagnosed with IUAs were enrolled in this trial.

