####  Control group.

2.5.2.

The control group received oral hormone supplementation for 3 menstrual cycles. The protocol was the same with oral hormone supplementation in the treatment group.

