### 2.6. Outcome measures

#### 2.6.1. Primary outcome.

a) Improvement of IUAs

The primary outcome of our study was the clinical response rate. After 2 menstrual cycles of treatment (about 2 months), hysteroscopy was performed to evaluate the recovery of endometrial cavity function. According to the recovery status, the clinical outcomes were classified into 3 levels (cure, improvement, and failure). These 3 stages had different standards. The first is the cure: after intrauterine treatment, the size and shape of the uterine cavity were normal, and the uterine angle and tubal opening were normal. The second is the improvement: IUAs score decreased after treatment. The severity of adhesions according to the American Fertility Society (AFS) IUA 19 classification.^[20]^ The last is the failure: they were unchanged clinical symptoms and a massive IUA condition. Overall response rate = (cure + improvement)/total number of cases *100%.

b)IUA evaluations

Before treatment, we evaluated and scored the severity of adhesions according to the American Fertility Society (AFS) IUA 19 classification.^[20]^ One of 2 reproductive surgeons in our hospital performed all operative hysteroscopies using the same techniques. During the operative hysteroscopy, the doctors then did hysteroscopic adhesiolysis for patients. Scores of 1 to 4 represent mild adhesions, 5 to 8 points for moderate adhesions, and 9 to 12 points for severe adhesions. Table 2 shows the details of the evaluation of IUA.

**Table 2 T2:** Score assessment of intrauterine adhesion.

**Evaluation variable**	**Score**

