### 2.12. Data entry and quality control of data

Data collection will begin once study participants are informed and enrolled. Data entry will be primarily electronic. To preserve confidentiality, data will be stored on secure servers and the authors had no access to information that could identify individual participants during or after data collection. All data analysis will be conducted with condition masked.

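### The title claims a placebo-controlled, single-blind trial, but the text describes no placebo or sham, patients cannot be blind, and no masking is described for the surgeons whose hysteroscopy decides the primary outcome

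*Protocol article*

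**What the plan says.** The title (Protocol article) gives the design as "Study protocol for a placebo-controlled, single-blind, single-center, randomized trial". Neither placebo nor blinding appears in the other design descriptions. The Abstract has "This study is a single-center, randomized controlled trial", section 2.2 has "This is a randomized, single-center clinical trial which aimed to evaluate the effectiveness of electrical stimulation combined with ultrasound acupuncture to treat IUAs", and the Discussion (section 3) likewise calls it a randomized, single-center trial.

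The control arm is set out twice. In the Abstract, women get the device plus hormone "or receive oral hormone supplementation only". In section 2.5.2, "The control group received oral hormone supplementation for 3 menstrual cycles", followed by "The protocol was the same with oral hormone supplementation in the treatment group".

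Section 2.5.1 gives the treatment arm the device plus that hormone regimen. Sessions last about 30 minutes. The current is raised until the woman can feel it, and vaginal stimulation by probe is added in cycles 2 and 3.

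The primary outcome (section 2.6.1) is cure or improvement at hysteroscopy after two cycles, where improvement is a decrease in the American Fertility Society (AFS) score with no minimum size. On who operates, the same section says "One of 2 reproductive surgeons in our hospital performed all operative hysteroscopies using the same techniques". On masking, section 2.12 says "All data analysis will be conducted with condition masked".

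**The concern.** The title tells a reader two things about protection against bias: that the device is compared with an inactive imitation, and that one party does not know the allocation. The body contradicts the first and does not explain the second.

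This matters because the primary outcome involves judgement. Extent and type of adhesions are graded by eye, and a single step down in any of the three items in Table 2 moves a woman from failure to improvement. If the person scoring knows the arm, small and well-meant differences in grading would count in favour of the device.

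The comparison also bundles the device with repeated clinic sessions that controls do not have. Without a sham, a difference cannot be attributed to the stimulation itself, which is what readers take a placebo-controlled result to show.

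**Working it through.** **Step 1. Is there a placebo?** Section 2.5.1 gives device plus hormone; section 2.5.2 gives hormone on the same regimen. The hormone is common to both arms and cancels from the comparison, so it cannot be a placebo for the device. No sham stimulation, inactive probe or placebo tablet is described. The contrast is device plus visits against no device.

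**Step 2. Who could be the blinded party?**

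| Party | What the article says | Can be blind? |
|---|---|---|
| Patient | Feels the current; vaginal probe in cycles 2 and 3; controls have neither (2.5.1, 2.5.2) | No |
| Staff giving the device | Apply pads and probe (2.5.1) | No |
| Surgeon at second look | One of two surgeons does all operative hysteroscopies (2.6.1); section 2.5 calls the second look an operative hysteroscopy | Not stated |
| Data analyst | Masked (2.12) | Yes |

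The sealed envelopes in section 2.4 conceal the allocation until assignment. Masked analysis acts after the scores exist. Neither covers the scoring.

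**Step 3. How easily can a score move?** Table 2 gives extent 1, 2 or 4, type 1, 2 or 4, and menstrual pattern 0, 2 or 4, a maximum of 4 + 4 + 4 = 12. The smallest step is 1 point, and any decrease counts as response.

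**Step 4. Reproduce the plan's own figure (section 2.9.1).** Inputs: control 56.6%, difference 20 points (so 76.6%), two-sided 5%, power 80%, unpooled variance.

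n = [p1(1−p1) + p2(1−p2)] × (1.960 + 0.842)² / d² = (0.2456 + 0.1792) × 7.849 / 0.04 = 83.4

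This rounds up to 84 per arm, 168 in total. With 20% loss, 84 / 0.8 = 105 per arm, 210 in total. The stated sample size reproduces, and the labelling problem does not affect it.

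**Step 5. Illustrate the exposure.** Assume no true effect, so the true rate is 56.6% in both arms. Let a fraction s of true failures in the device arm only be scored as improvement. The observed device rate is 0.566 + 0.434 × s. The last two columns give the exact probability, by enumerating both binomials, that the chi-square test (pooled, without continuity correction) is significant at two-sided 5% in favour of the device.

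| s (assumed) | Device rate | 84 per arm | 105 per arm |
|---|---|---|---|
| 0 | 56.6% | 2.6% | 2.4% |
| 2% | 57.5% | 3.3% | 3.2% |
| 5% | 58.8% | 4.8% | 4.9% |
| 10% | 60.9% | 8.3% | 9.3% |
| 20% | 65.3% | 20.8% | 25.6% |
| 30% | 69.6% | 41.5% | 50.7% |

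The fractions s are not in the documents. At s = 20% the spurious difference is 0.434 × 0.20 = 8.7 points, under half of the 20 points the trial is sized to detect.

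**The case against.** The strongest reply is that silence is not evidence. A journal article condenses the full protocol, and section 2.6.1 does not say that the two surgeons know the allocation. Section 2.4 has the study site open the envelopes and section 2.5.1 has doctors apply the device, but neither identifies these people as the surgeons. Since patients cannot be blind, a masked assessor is one natural meaning of single-blind. That stands. A reader might infer that the surgeons are unmasked; the article supports only that no masking of them is described.

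A reader might also infer that the trial has no protection against bias at all. That goes too far: allocation is by sealed, ordered envelopes and the analysis is masked. The gap is confined to patients and to outcome scoring.

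Two further points stand. The article lists menstrual pattern as a score item but does not say how it is obtained, so self-report by an unblinded patient is plausible rather than stated; the other two items make up 8 of the 12 points. The illustration also rests on assumed upgrading in one arm only, and at 2% or 5% the effect is small. It shows sensitivity and is not evidence that bias will occur.

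None of this rescues the placebo label. Section 2.5.2 does not leave the control arm to another document; it defines it, in conflict with the title.

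**Conclusion.** The point holds in this form. The placebo-controlled label is contradicted by the Abstract and by sections 2.5.1 and 2.5.2. Single-blind cannot refer to the patients, and the article names no blinded party other than through masked analysis. No masking is described for the hysteroscopic scoring on which the primary outcome depends.

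The placebo contradiction and the patients' lack of blinding follow directly from the text and need no assumption. Whether the scoring surgeon is masked is an open question that one sentence could settle. If the surgeon is not masked, the possible cost ranges from negligible to serious. On the assumptions of no true effect, one-sided upgrading and 84 per arm, the chance of a false finding for the device goes from 2.6% to about 3% at 2% upgrading and to about 42% at 30%.

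**What to change.** 1. **Title and design wording.** Remove 'placebo-controlled'. Describe the trial as an add-on comparison without sham, open-label for patients, and limit the conclusion to the device package with its visits against no device. Keep 'single-blind' only if the blinded party is named and is not the patient.
2. **Section 2.6.1.** Require that the second-look hysteroscopy be scored by one of the existing two surgeons who is not told the arm, with extent and type of adhesions recorded before the menstrual history or treatment file is seen. If this is already the practice, say so.

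The cost is a less favourable design label and some scheduling burden; no extra staff or procedure is needed and the sample size stays as it is. If the surgeon who did not do the first operation is used, baseline and follow-up scores come from different raters. Between-rater differences then enter every change score and add noise, but they should do so equally in both arms and so should not favour either.

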## Abstract

**Methods::**

This study is a single-center, randomized controlled trial. A total of 210 patients with IUAs will be randomly assigned into 2 groups according to the ratio of 1:1, as the treatment group and the control group. Participants will receive the electrical muscle stimulation combined with ultrasound acupuncture therapy and oral hormone supplementation or receive oral hormone supplementation only. The primary outcome was the clinical response rate. There were 3 menstrual cycles of treatment and 3 menstrual cycles of follow-up in this study.

**Ethics and Dissemination::**

This study protocol was approved by the Ethics Committee of the Reproductive Hospital of Guangxi Zhuang Autonomous Region (approval number: KY-LL-2022-06). This trial will be conducted in accordance with the principles of the Declaration of Helsinki as well as Good Clinical Practice. Study results will be disseminated at academic presentations and publications in peer-reviewed journals.

**Trial Registration::**

Registry name: Clinical value of electroultrasonic instrument in the treatment of IUAs and changes of related protein expression; Registry number: ChiCTR2200058901; registration date: April 19^th^, 2022; http://www.chictr.org.cn/showproj.aspx?proj=166155.

Strengths and limitations of this study•Observational studies have evaluated the effectiveness of prevention of recurrence of IUAs before, but the quality of evidence on the effectiveness of the ULTRA-EMS therapy device in improving reproductive outcomes of IUAs is still unsatisfactory.•This study will evaluate the effectiveness of the ULTRA-EMS therapy device in preventing the recurrence of IUAs after operative hysteroscopy. It will improve the quality of the evidence on the effectiveness of the ULTRA-EMS therapy device preventing the recurrence of IUAs and improving reproductive outcomes after operative hysteroscopy.•Recurrence of postoperative adhesions is one of the most important factors for poor reproductive outcomes after operative hysteroscopy. This therapy will help decrease the recurrence of IUAs and improve reproductive outcomes.

## 1. Introduction

Intrauterine adhesions (IUAs) were first reported by Fritsch in 1894.^[1]^ In 1950, Asherman systematically and comprehensively reported IUA through a summary of 29 IUA cases, so that people began to pay attention to and deeply studied this disease. Also, the IUAs is also known as Asherman syndrome.^[2]^ It is characterized by varying degrees of scar formation in the uterine cavity and is also the cause of menstrual disorders, infertility, and placental abnormalities.^[3,4]^ IUA occurs most often after infection or trauma, such as uterine surgery, especially in the postpartum period of cesarean section.^[5,6]^ A large number of inflammatory chemokines, together with cytokines and cell adhesion molecules, are aberrantly expressed during the development of IUA.^[7]^ The current report found that IUA was associated with decline in reproductive clinical outcomes after natural conception and assisted reproductive technologies.^[8]^ The prevalence of IUAs is currently not entirely consistent, ranging from 0.3% (an incidental finding in women with intrauterine device placement without gynecological symptoms) to 21.5% (women with postpartum curettage).^[9]^ Of all the tools used to diagnose IUA or evaluate the severity of IUA, hysteroscopy is the current gold.^[10]^ In the treatment, the recovery of uterine shape and function is mainly helped by surgical separation of the adherent uterine cavity, supplemented by physical isolation and hormone to promote endometrial regeneration.^[8]^ Operative hysteroscopy is also considered a good treatment for patients.^[11]^ The postoperative effectiveness of hysteroscopic separation of IUAs is generally satisfactory, and the probability of usual or improved menstruation after surgery can reach 92% to 96%.^[12]^ Recurrence of postoperative adhesions is one of the most important factors for poor reproductive outcome after operative hysteroscopy, especially in cases diagnosed with severe AS, where the recurrence rate is significantly higher.^[13]^ More and more scholars have focused on exploring the measures to prevent adhesion recurrence and improve postoperative pregnancy rate during and after operative hysteroscopy.^[10]^

Electrical stimulation, including Neuromuscular Electrical Stimulation (NMES) and transcutaneous electrical nerve stimulation (TENS), has been applied in the treatment of stress urinary incontinence, pelvic pain, and sexual dysfunction.^[14]^ Some researchers also did a preliminary study of NMES in reproductive medicine and have improved the clinical pregnancy rate.^[15]^ The mechanism of action in NMES and TENS is related to the mechanism of recurrence of IUAs. Acupuncture has many applications in treating various reproductive disorders, such as polycystic ovary syndrome, pain induced by oocyte retrieval, diminished ovarian reserve, embryo transfer, and oligospermia/asthenospermia.^[16–18]^ Some observational studies have evaluated the effectiveness of prevention of recurrence of IUAs.^[19]^ The electrical muscle stimulation combined with ultrasound acupuncture (ULTRA-EMS) therapy device C7000 (Nanjing Medlander Medical Technology Co. Ltd, Nanjing, China), combined TENS, NMES, and ultrasound acupuncture and has been used for reproductive medicine. Nevertheless, this combination has not been evaluated for the treatment or prevention of recurrence of IUAs after operative hysteroscopy.

This study aims to evaluate the effectiveness of ULTRA-EMS in preventing the recurrence of IUAs after operative hysteroscopy.

## 2. Methods

### 2.1. Objectives

This trial is aimed to evaluate the effectiveness of the ULTRA-EMS therapy device in preventing the recurrence of IUAs and improving reproductive outcomes after operative hysteroscopy.

### 2.2. Study design

This is a randomized, single-center clinical trial which aimed to evaluate the effectiveness of electrical stimulation combined with ultrasound acupuncture to treat IUAs. This randomized trial was conducted in one single center: Guangxi reproductive hospital. A total of 210 patients diagnosed with IUAs were enrolled in this trial.

### 2.3. Participants

Patients were recruited only if they met all inclusion criteria and did not meet the exclusion criteria. Figure 1 is flow diagram of enrollment of study participants.

**Figure 1. F1:**
[figure not shown]
Schedule of enrolment, interventions, and assessments.

Inclusion criteria:

(1) Female aged between 20 and 40 years;(2) According to practice guidelines on IUAs developed in collaboration with the European Society of gynecological endoscopy (esge), hysteroscopy is the most accurate method for diagnosis of IUAS,^[12]^ and we diagnosed the IUAS with hysteroscopy;(3) Patients were willing to accept hysteroscopic adhesiolysis;(4) Regular menstrual cycle;(5) Sign informed consent.

Exclusion criteria:

(1) Acute and subacute genital inflammation and pelvic infection;(2) Uterine perforation repair within 6 months;(3) Cervical cancer, adenomyosis, uterine fibroids (nonsubmucosal) > 4 cm, endometrial cancer, and other uterine tumors;(4) Genital tract tuberculosis, without antituberculosis treatment;(5) Suffering from serious diseases: such as heart, lung, liver, kidney and other medical diseases, coagulation dysfunction and bleeding disorders, difficulty tolerating surgery;(6) Taking hormone drugs in the past 1 month;(7) Combined with endocrine-related diseases (such as ovarian dysfunction, thyroid disease);(8) Patients with moderate and severe IUAs after 2 or more intrauterine adhesiolysis.

### 2.4. Randomization and participants allocation

Block randomization was used in this study with a block size of 4. A randomization table (containing randomization information including random seeds, block length, and number) was generated by the statistical professional of the Clinical Research Institute of Shanghai Jiao Tong University School of Medicine based on the block randomization method. The randomization table will be sealed in duplicate and will be kept by the primary research institution undertaking the clinical trial (the filled-in randomization table shall not be opened before the end of the question). At the same time, a corresponding randomization letter was prepared for each subject. The envelope will be labeled with the subject number. The sealed envelope indicated the assigned treatment for the issue, and the statistical unit was responsible for sending the randomization letter to the study site. The study site must open the sealed stationery in the order of the cases and dispose of them according to the randomly assigned group in the paper and the corresponding treatment. The opening date and time should be recorded and signed by the sponsor.

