Electrical stimulation combined with ultrasound acupuncture therapy is as follows: the device is called ULTRA-EMS THERAPY DEVICE MLD C7000 (Nanjing Medlander Medical Technology Co. Ltd, Nanjing, China). During the menstrual cycle, Patients would be treated with TENS and ultrasound acupuncture modalities for 7 days from the first day after the patient undergoes hysteroscopic adhesion release. Each patient visit lasted approximately 30 minutes. TENS includes 8 electrode pads, which correspond to different body positions, as shown in the figure below. Table 1 shows the TNES and acupuncture points. The electrode piece used for TENS is a body surface electrode-circular 50 mm (viscose electrode piece), which is reusable and specially used by specially assigned persons. It is discarded after ten times of use. Stimulation current intensity is as follows:: adjustable within the range of 0 to 100 mA, adjustable with the step of 0.5 mA. Intensity adjustment is based on the patient’s tolerance to the degree that the patient can feel the current stimulation. When the patients accept TENS, the doctors put electrode pieces on the surface of the body (S1-8). The ultrasound acupuncture includes a therapeutic ultrasound probe and ultrasonic therapy fixing paste. Therapy fixing paste is used for applying an ultrasonic probe to acupoints on the body surface (A1-8). The ultrasound acupuncture mode has 10 shifts with adjustable and effective sound intensity: less than 3 W/cm^2^. Typically, we used the sixth shift for patients. During the 2 to 3 menstrual cycle, TENS, ultrasound acupuncture, and intermittent vaginal electrical stimulation would be used for patients from 5 to 7 days of the menstrual cycle. TENS and ultrasound acupuncture are the same as the first menstrual cycle. Intermittent vaginal electrical stimulation is as follows: all women had their own vaginal probe (Nanjing Medlander Medical Technology Co. Ltd, Nanjing, China, MLD CV01). Doctors applied ointment (conductive gel) to the probe tip prior to insertion into the vagina and inserted the stylet approximately 6 to 8 cm deep. An adhesive electrode will be placed on the skin outside the vagina (on the female thigh). The vaginal probe will be left in the vagina, and electrical stimulation was started. The selected parameters included a biphasic intermittent biphasic current with a frequency of 40 Hz, a pulse width of 250 us, and a current intensity between 0 and 120 mA. On-off (duty cycle) periods were individually adjusted based on each female’s ability to maintain voluntary contractions. TENS, ultrasound acupuncture, and intermittent vaginal electrical stimulation would last about 30 minutes every time.

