### 2.9. Statistical considerations

#### 2.9.1. Sample size estimation.

The number of patients required for this trial was determined on the basis of the primary outcome of the clinical response rate. With an estimated clinical response rate of 56.6% in the control group, we calculated that 168 participants would be required for the trial to achieve 80% power (β = 0.2) to detect a 20% difference in a clinical response rate increase in the trial groups. The allocation ratio was 1:1, at a 2-sided overall significance level of 5% (α = 0.05). The test statistic used was the 2-sided Z-Test with unpooled variance. With an estimated follow-up loss of 20%, we aimed to recruit 105 participants per group, which was 210 participants in total.

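### A single fixed block size of 4 at one unstratified site, with past assignments visible to treating staff, could make about one third of assignments certain in advance

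*Protocol article*

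**What the plan says.** Section 2.4 of the protocol article fixes the allocation method: "Block randomization was used in this study with a block size of 4". Section 2.9.1 gives a 1:1 ratio, so each block holds two of each arm. The list comes from an outside statistical unit. Numbered sealed envelopes go to the site, and "The study site must open the sealed stationery in the order of the cases"; the opening date and time are to be recorded and signed. On custody, the section says: "The randomization table will be sealed in duplicate and will be kept by the primary research institution undertaking the clinical trial". It also says that the table is not to be opened early.

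Section 2.2 states: "This randomized trial was conducted in one single center: Guangxi reproductive hospital". No stratification factor is described, so the site works through one continuous sequence.

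The title calls the study a "placebo-controlled, single-blind, single-center, randomized trial". The arms nevertheless look different to those who treat. In the treatment group (section 2.5.1) doctors attach the electrodes and, in later cycles, insert a vaginal probe. For controls, section 2.5.2 says: "The control group received oral hormone supplementation for 3 menstrual cycles". It describes no sham device. The only masking stated outside the title is that of the data analysis (section 2.12).

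**The concern.** When the block size is constant and past assignments are visible, the rest of a block can be worked out by counting. With one site and one list, the block ends are also known: they fall at cases 4, 8, 12 and so on. Sealing the envelopes prevents reading ahead but does not prevent deduction.

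Two decisions come before or around allocation and involve judgement. One is whether, and when, to enrol a given patient. The other is the baseline AFS adhesion score, assigned at hysteroscopy by one of two surgeons at the hospital (section 2.6.1). That score matters twice. It measures severity, and it is the reference value for the primary outcome, because improvement means a fall from the patient's own baseline. Treatment starts on the day of adhesiolysis (section 2.5.1), and section 2.4 does not say that the envelope is opened only after the score is recorded.

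The primary comparison in section 2.9.2 is a chi-square or Fisher's exact test. Neither would correct a severity imbalance produced by selective enrolment.

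**Working it through.** **Inputs.** Block size 4 (section 2.4); 1:1 ratio and 210 participants (section 2.9.1); one centre (section 2.2).

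**The plan's own figure.** The article gives no figure for predictability. Its sample size reproduces: with 56.6% against 76.6% and the unpooled Z formula, n = [0.566 × 0.434 + 0.766 × 0.234] × (1.960 + 0.842)² / 0.20² = 83.4. That is 84 per arm and 168 in total, and 168 / 0.8 = 210. The present point does not change it.

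**Assignments certain in advance, fixed block of 4.** There are 6 equally likely orders of two and two.
- Positions 1 and 2 are never certain.
- Position 3 is certain when the first two match: 2 of 6 orders, probability 1/3.
- Position 4 is always certain: probability 1.
- Sum: 1/3 + 1 = 4/3 per block; (4/3) / 4 = 33.3%.
- Over 210 participants there are 52 full blocks plus 2 participants in positions 1 and 2: 52 × 4/3 = 69.3, so about 69 of 210 (33.0%).

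**Best-guess rate.** The rule is to guess the arm that is behind in the block, and to toss a coin when the arms are level.
- Position 1: 1/2.
- Position 2: 2/3.
- Position 3: (1/3) × 1 + (2/3) × 1/2 = 2/3.
- Position 4: 1.
- Sum: 2.833 of 4 = 70.8% per full block.
- Over 210: (52 × 2.833 + 1/2 + 2/3) / 210 = 148.5 / 210 = 70.7%.

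**Alternatives.** Fixed blocks of 6 and 8 were enumerated in the same way. Mixed sizes were simulated (3,000 runs of 210, each size equally likely), with a guesser who knows the set of sizes but is not told the block ends and updates after each assignment.

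| Scheme | Certain in advance | Best-guess rate |
|---|---|---|
| Fixed 4 | 33.3% | 70.8% |
| Fixed 6 | 25% | 68.3% |
| Fixed 8 | 20% | 66.6% |
| Mixed 4/6 | 5.4% | 69.3% |
| Mixed 2/4/6 | 4.1% | 70.2% |
| Mixed 4/6/8 | 2.3% | 68.0% |

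The simulation returned 33.0% and 70.7% for fixed blocks of 4, in agreement with the exact values over 210. Mixing removes nearly all certainty but lowers average guessability only a little.

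**The case against.** The allocation procedure has real safeguards: an outside unit makes the list, envelopes are sealed and numbered, openings are logged, and the table is sealed. The article does not say who at the site is told the block size, so the one-third figure is conditional. This stands, and the point is worded accordingly.

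Several stronger readings are tempting but not supported.
- **Custody gives staff the list.** The table is sealed and not to be opened early, and the holding institution is not named, although in a single-centre trial it is probably the hospital. Custody adds nothing to the one-third figure.
- **The trial is simply unmasked.** The title says single-blind without naming the blinded party. The text supports only that treating staff see the assignment.
- **Publication disclosed the block size to recruiters.** No recruitment dates are given and the tenses are mixed, so recruitment may already have been over.
- **Selection bias passes straight into the result.** The Introduction links severe disease with more recurrence, but response counts any fall from the patient's own baseline score. Severe cases may recur more and also have more room to fall. Neither the size nor the direction of a bias in the response rate is established.
- **The missing adjustment is itself a defect.** Adjusted analyses may be in an analysis plan that is not shown. What can be said is that the primary test as stated is unadjusted.

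What remains is that the article itself fixes a predictable scheme in a setting where prediction is easy.

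**Conclusion.** The point holds as a preventable risk that is cheap to reduce. A fixed block of 4 leaves about one third of assignments (about 69 of 210) certain in advance and gives a best-guess rate of 70.8%. This assumes that enrolling staff know the block size and follow past assignments, which one unstratified sequence with visibly different arms makes easy. The arithmetic is exact. The consequence is only possible: foreknowledge could bias enrolment by severity or the baseline AFS score, but the documents do not show that it did. The change is advisable, but the point does not invalidate the trial.

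**What to change.** 1. **New list for participants not yet randomised.** The statistical unit issues it with randomly mixed block sizes, for example 4, 6 and 8, that are not disclosed to the site. It takes over at a block boundary of the present list.
2. **Order of steps.** Open each envelope only after eligibility and the baseline AFS score have been recorded. This matters because the best-guess rate stays near 68% even with mixed blocks.
3. **Custody, as a secondary safeguard.** Keep the sealed table at the statistical unit.
4. **Analysis, whether or not recruitment is complete.** Adjust the primary comparison for baseline AFS class (mild, moderate, severe). This covers measured severity only. It cannot correct selection on unrecorded features or a baseline score that was itself influenced.

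**Cost.** One new list and envelope set from the same unit, and a documented change of procedure if recruitment is under way. The arms may differ by up to 4 if recruitment stops inside a block of 8, or by up to 2 + 4 = 6 if the present list is also cut inside a block of 4, which is the reason to switch at a boundary.
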